### Data management

Data will be collected on paper and will be temporarily stored in a safe location at the University of Maastricht. Subsequently, after digitalizing, the data will be stored for 15 years in the research department of the Maastricht University Medical Center. We will use MACRO to digitalize all data.

### Statistical analysis

Baseline characteristics include age in years, ethnic background, gravidity and parity, gestational age at birth, mode of birth in this pregnancy, and if applicable, mode of previous birth and experience of previous birth(s). The primary outcome EA, and its association with continuous care versus care-as-usual, will be analyzed using multilevel logistic regression analysis.

The secondary outcomes are listed in Table 2, and will be addressed using multilevel linear regression analyses (for continuous variables), multilevel logistic regression (for binary variable variables) or multilevel multinomial logistic regression analysis (for categorical outcomes with more than two categories). If important baseline characteristics will differ greatly between the study arms, we will include them in the analysis. Missing data will be imputed by use of stochastic regression imputation, with predictive mean matching as the imputation model. We will perform both an intention to treat analysis and per protocol analysis. Cost-effectiveness will be calculated for the six-week period following childbirth and incremental cost effectiveness ratios will be calculated in QALY per prevented EA based on utility index from the EQ5D and usage of healthcare. Standardized sensitivity analysis will be carried out to quantify the outcome. A budget impact analysis will be performed using ISPOR guidelines, which take into account the financial consequences of the implementation of maternity care assistants as providers of continuous support during labor.

**Table 2 Tab2:** Secondary Outcome Measures

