In the Netherlands, midwives provide pregnancy, birth and postnatal care to healthy, low-risk women. These women can choose to give birth at home or in a hospital. Based on national guidelines [11], a risk assessment is performed for each pregnant woman during pregnancy and delivery. This risk assessment can result in transfer of care between midwife and obstetrician at any time during pregnancy or delivery. Maternity care assistants (MCAs) assist the midwife during the last part of the first stage and in the second stage of birth. For both low- and high-risk women, midwives and MCAs provide home care following hospital discharge, for the first week of the postnatal period.

Currently, the resources are not available to provide continuous care to all women during labor in routine midwifery- or obstetric-led care. In fact, continuous care is provided in less than 30% of all cases [12]. At the same time, nationwide, there has been a steep rise in the use of epidural analgesia (EA) amongst primiparous women, from 17% in 2006 to 43% in 2018. In our region, more than half of all women delivering their first baby uses EA. [12] EA is associated with transfer of care, maternal fever, an increased risk of an instrumental delivery, and admittance of the baby due to antibiotic treatment [13]. These outcomes also result in a considerable rise in costs. We hypothesize that adding MCAs to standard maternity care for the provision of continuous support during delivery will be a cost-effective intervention. We predict that any extra costs associated with providing this care will be outweighed by the savings associated with the reduction in EA use. Finally, we predict that the intervention will not decrease patient satisfaction or lead to an increase in complications.

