### Sample size calculation

We calculated that, in order to be able to detect a reduction in use of EA from 25 to 17% (with an alpha 0.05 and beta 0.20), taking into account the use of multilevel analysis (10% higher sample size) and an attrition of 10% (90% complete records), a sample size of 2 × 496 participants will be necessary (*n* = 992).

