**Maternal outcome**	
Mode of delivery	
3th or 4th degree perineal tear	
Use of pain medication other than Epidural Analgesia	
> 1000 cc blood loss	
Blood transfusion	
Fever during labor	
Use of antibiotics	
Proven infection	
Uterine rupture	
Intensive Care (IC) admittance	
Maternal death	

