**Neonatal outcome**	
Need for admittance to hospital	
Neonatal Intensive Care Unit (NICU) admittance	
Apgar below 7	
Neonatal death	

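### Multilevel logistic regression is assigned to harms so rare that an arm may well have no events, and the odds ratio then has no usable interval

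*Protocol article*

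**What the plan says.** The Statistical analysis section of the protocol article states: "The secondary outcomes are listed in Table 2, and will be addressed using multilevel linear regression analyses". That first model is meant for outcomes on a continuous scale. Binary outcomes are given "multilevel logistic regression (for binary variable variables", and a multinomial version is kept for outcomes with three or more categories. The choice of model depends only on the type of variable. No minimum event count, exact or penalised method, risk difference or counts-only rule is given.

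The outcomes covered by the rule are named in Table 2. Under maternal outcomes they include "Uterine rupture", "Intensive Care (IC) admittance" and "Maternal death"; under neonatal outcomes, "Neonatal death". The article gives no expected rate for any of them.

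Two other statements bear on the point. The sample size section plans 496 women per arm and allows for "an attrition of 10% (90% complete records". The Background says "we predict that the intervention will not decrease patient satisfaction or lead to an increase in complications".

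**The concern.** The four harms are the most severe on the list and probably among the rarest. With about 500 women per arm, a harm occurring in one or two women per thousand is expected less than once per arm, so an empty arm is an ordinary result.

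Ordinary maximum likelihood then fails:

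- If only the continuous-care arm is empty, the odds ratio estimate is zero.
- If only the care-as-usual arm is empty, it is infinite.
- If both are empty, it is not identified.

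A random intercept does not remove this separation. The Wald interval is useless in all three cases. A profile-likelihood interval is only a partial rescue: it has an upper limit when continuous care alone is empty, and none when care-as-usual is empty, which is where excess harm under the intervention is the question.

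With so few events no test will settle anything. The useful result is the count in each arm and an interval for the excess that remains possible. That interval bears on the Background's prediction about complications, and the assigned model often cannot supply it.

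**Working it through.** **Inputs.** From the article: 496 per arm, 10% attrition, multilevel logistic regression for binary Table 2 outcomes, and the four named harms. Assumed, because the article gives none: event rates from 0.01% to 1%, equal in both arms. The four harms need not share one rate.

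**The plan's own figure.** For 25% versus 17%, two-sided alpha 0.05, power 0.80, pooled-variance formula:

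n = [1.960 × √(2 × 0.21 × 0.79) + 0.842 × √(0.25 × 0.75 + 0.17 × 0.83)]² / 0.08² = 406 per arm.

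406 × 1.10 / 0.90 = 496.2, which reproduces 496. The sample size is not in dispute. After 10% attrition, 0.9 × 496 gives about 446 per arm.

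**Chance of an empty arm.** With event rate p and n women per arm, q = (1 − p)^n. Then P(care-as-usual empty) = q, P(both empty) = q², P(at least one empty) = 1 − (1 − q)², and P(care-as-usual empty, continuous care with at least one event) = q(1 − q). For example, at p = 0.001 and n = 496, q = 0.999^496 = 0.609 and 1 − 0.391² = 0.847.

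| n per arm | Assumed rate | Expected events per arm | At least one empty | Care-as-usual empty | Both empty | Care-as-usual empty, continuous care ≥ 1 |
|---|---|---|---|---|---|---|
| 496 | 0.01% | 0.05 | 99.8% | 95% | 91% | 5% |
| 496 | 0.1% | 0.50 | 85% | 61% | 37% | 24% |
| 496 | 0.2% | 0.99 | 60% | 37% | 14% | 23% |
| 496 | 0.5% | 2.48 | 16% | 8% | 0.7% | 8% |
| 496 | 1% | 4.96 | 1.4% | 0.7% | 0.0% | 0.7% |
| 446 | 0.1% | 0.45 | 87% | 64% | 41% | 23% |
| 446 | 0.2% | 0.89 | 65% | 41% | 17% | 24% |
| 446 | 0.5% | 2.23 | 20% | 11% | 1.1% | 10% |

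With 496 per arm, the chance of at least one empty arm passes 50% below a rate of 0.25%. The chance of an empty care-as-usual arm does so below 0.14%.

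**What the model returns.** For a single-level logistic fit with 1 event under continuous care and 0 under usual care, the log odds ratio is still diverging at 20.4, with standard error about 16,000 and p = 0.999. The profile log-likelihood flattens at −7.206 as the odds ratio grows, so no upper limit exists. Splits of 2–0, 3–0, 0–1, 0–2 and 0–3 behave in the same way.

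**Intervals, 496 per arm, continuous care minus usual care.**

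| Events (continuous care–usual care) | Profile-likelihood 95% odds ratio | Newcombe 95% risk difference, points |
|---|---|---|
| 0–0 | not identified | −0.77 to 0.77 |
| 1–0 | 0.17 to infinity | −0.58 to 1.13 |
| 2–0 | 0.62 to infinity | −0.42 to 1.46 |
| 3–0 | 1.12 to infinity | −0.26 to 1.76 |
| 0–1 | 0 to 5.82 | −1.13 to 0.58 |
| 0–2 | 0 to 1.61 | −1.46 to 0.42 |
| 0–3 | 0 to 0.89 | −1.76 to 0.26 |

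A Firth-penalised fit is also finite but wide: 3.0 (0.12 to 74), 5.0 (0.24 to 105) and 7.0 (0.36 to 137) for 1–0, 2–0 and 3–0.

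**Tests.** For all events in one arm, with totals of 1, 2 and 3, the likelihood-ratio p is 0.239, 0.096 and 0.041, against Fisher exact p of 1.000, 0.499 and 0.249. The 3–0 result shows that a likelihood-ratio test can be too optimistic for a single table. Its overall type I error at nominal 5% is 0.3% at a rate of 0.05%, 1.7% at 0.1% and 5.9% at 0.2%, so no general inflation is claimed at these rates.

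**The case against.** The strongest reply is that a condensed article names a family of models by type of variable and leaves sparse tables to the full protocol or analysis plan. It states neither estimator nor interval, and a penalised or Bayesian fit would still be multilevel logistic regression. The estimator is indeed unstated, so the failure is conditional on ordinary maximum likelihood. But the article assigns the model to outcomes it names, without exception, and nothing in it calls for penalisation. A plan that followed the text would inherit the problem.

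Four further points stand in part:

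- The probabilities for an empty care-as-usual arm include tables with no events at all. The pattern that would cause concern, events only under continuous care, has probability 5%, 24% and 23% at 0.01%, 0.1% and 0.2%. The odds ratio lacks an upper limit in both situations.
- All rates are assumed. Intensive care admission may be common enough to escape the problem.
- The four harms appear only in Table 2, not in the numbered list under Study outcomes, and the prediction about complications may rest mainly on commoner events.
- The gain is modest. An upper limit of 0.77 points is nearly four times an assumed rate of 0.2%, and a diverging fit is obvious to the analyst. Even so, a bounded interval chosen in advance is better than a method improvised after the fit fails.

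**Conclusion.** The concern holds as a minor point. The stated rule, fitted by ordinary maximum likelihood, gives no usable effect estimate for any listed harm with an empty arm, and no upper limit on the odds ratio when care-as-usual is empty. For a harm at 0.2% or less, at least one empty arm is more likely than not (60% or more with 496 per arm); at 0.5% the chance is 16% and at 1% about 1%. These figures assume equal rates in both arms. What is lost is a reportable bound on excess harm. The primary analysis, the commoner binary outcomes and the sample size are untouched.

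**What to change.** Add one sentence to the Statistical analysis section. Multilevel logistic regression is kept for binary outcomes that reach a minimum event count fixed in advance, for example 10 in total and at least one per arm. For rarer harms, report counts per arm and the risk difference with an exact or score-type 95% interval (Newcombe or Miettinen–Nurminen). Add a Fisher exact p-value or Firth-penalised logistic regression only if a test or adjustment is wanted. An exact conditional odds ratio would not do instead, because it too has no upper limit when care-as-usual is empty.

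The change needs only standard software and events already recorded. The price is that the rare-event results ignore clustering and covariates, which zero to three events could not support in any case.

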### Data collection

Data will be collected at three moments in time (Table 1). Baseline demographic and obstetric characteristics will be collected before randomization. At this point, the questionnaire also includes:
The EQ5D, a standardized validated instrument measuring five health dimensions (mobility, self-care, daily activities, pain and discomfort, and anxiety and depression) that allows us to asses health in individuals or populations [15, 16];The Cambridge Worry Scale (CWS), a validated instrument used to measure the extent and content of worries in specific situations (socio-medical, own health, socio-economic and relational) [17];The State-Trait Anxiety Inventory (STAI) questionnaire, a validated instrument that measures two types of anxiety: state and trait [18, 19].

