**Table 1 Tab1:**
[figure not shown]
Timeline and Data Collection. EQ. 5 D Standardized validated instrument measuring five health dimensions. STAI State-Trait Anxiety Inventory

*Control of in- and exclusion criteria (i.e. reason for removal from study: elective caesarean because of breach position).

*EQ5D* Standardized validated instrument measuring five health dimensions; *STAI* State-Trait Anxiety Inventory; *CWS* Cambridge Worry Scale; *LAS* Labor Agentry Scale; *CLIK-Q* Questionnaire to reflect on patient satisfaction (maternity empowerment/experience)

In the first week after birth (preferably the same day of the birth), the MCA will fill-out a case report form together with the midwife or doctor, based on primary and secondary outcome measures. Additionally, the woman will fill out the Labor Agentry Scale (LAS) questionnaire, which scores experience of personal control during labor. In field studies, the LAS showed an inverse relationship between anxiety and control [20].

Six weeks after birth, the participants will fill out the final questionnaire, the CLiK questionnaire, used within Dutch maternity care agencies to reflect on patient satisfaction. It is based on the validated Maternity Empowerment Questionnaire. Questions are about maternity empowerment, the EQ5D and women’s experiences with maternity care assistance. We will perform random checks of the completed case reports and we will extract data from the main source if there are inconsistencies in completed case report forms.

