**Questionnaires**	
EQ 5D^a^State-Trait Anxiety Inventory (STAI)	
Cambridge Worry Scale (CWS)	
Labor Agentry Scale (LAS)	
CLIK-Q^b^	

^a^ Standardized validated instrument measuring five health dimensions

^b^ Questionnaires to reflect on patient satisfaction (maternity empowerment and experience)

One hour of care provided by an MCA costs approximately 45 euros, and we expect extra costs of approximately 225 euros per woman for the provision of continuous care. The costs for one EA, when taking complications into consideration, is approximately 2200 euros. We would therefore expect the use of continuous care to be cost effective with just a 10% reduction in EA use.

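### Baseline EQ-5D should always be a covariate for the six-week EQ-5D outcome, not one that enters only after a large observed imbalance

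*Protocol article*

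**What the plan says.** All points are from the protocol article.

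- **Baseline measurement (Data collection).** "Baseline demographic and obstetric characteristics will be collected before randomization. At this point, the questionnaire also includes" three instruments, of which the first is "The EQ5D, a standardized validated instrument measuring five health dimensions".
- **Follow-up measurement (text after Table 1).** The six-week questionnaire carries the same instrument: "Questions are about maternity empowerment, the EQ5D and women’s experiences with maternity care assistance".
- **Outcome status (Table 2, Questionnaires).** EQ-5D is listed among the secondary outcome measures. Statistical analysis also makes its utility index the basis of the QALYs, over the six weeks after birth.
- **Model (Statistical analysis).** Continuous secondary outcomes are assigned multilevel linear regression. No baseline value of an outcome is named as a covariate.
- **Covariate rule (Statistical analysis).** "If important baseline characteristics will differ greatly between the study arms, we will include them in the analysis". Neither importance nor the size of difference that counts is defined.
- **List of baseline characteristics (Statistical analysis).** "Baseline characteristics include age in years, ethnic background, gravidity and parity, gestational age at birth, mode of birth in this pregnancy", followed by mode and experience of earlier births. EQ-5D is not named.

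**The concern.** The value of a baseline covariate in a randomized comparison comes from how well it predicts the outcome, not from whether the arms happen to differ on it. The pre-randomization score on the same instrument is a natural candidate for predicting the six-week score, and here it is already collected. A rule that admits covariates only after a large observed difference has two weaknesses for this outcome. It will seldom be triggered in a trial of this size, so most of the available precision goes unused. And because no threshold is fixed, the choice of model is made after the data are seen.

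At stake are the width of the confidence interval for the EQ-5D difference and, if the QALY comparison is handled in the same way, the precision of a QALY difference that must be small over six weeks.

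**Working it through.** **1. The plan's own figure.** Inputs from Sample size calculation: 25% versus 17%, alpha 0.05 (taken as two-sided), power 0.80, 10% for multilevel analysis, 10% attrition. With pooled variance under the null:

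n = [1.96·√(2·0.21·0.79) + 0.842·√(0.25·0.75 + 0.17·0.83)]² / 0.08² ≈ 406 per arm

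406 × 1.10 / 0.90 = 496.2, so the stated 496 per arm is reproduced. It concerns epidural use only. The article gives no target effect, SD or correlation for EQ-5D.

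**2. How often the rule would be triggered.** Complete records per arm: 0.90 × 496 ≈ 446. SD of the chance difference in baseline means: √(2/446) = 0.067 SD, with a 95% limit of 1.96 × 0.067 = 0.131 SD. Taking out the 10% multilevel allowance (406 per arm) gives √(2/406) = 0.070. The threshold has to be assumed:

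- Read as p < 0.05, the rule fires in 5% of randomizations.
- Read as 0.2 SD, it needs z = 0.2/0.067 ≈ 3.0, which occurs in about 0.3%.

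**3. What always adjusting would give.** The variance of the adjusted difference is (1 − rho²) times the unadjusted variance. Because rho is not in the documents, a range is shown:

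| rho (assumed) | 1 − rho² | fall in standard error, 1 − √(1 − rho²) | equivalent unadjusted n per arm, 446/(1 − rho²) |
|---|---|---|---|
| 0.1 | 0.99 | 0.5% | 451 |
| 0.3 | 0.91 | 4.6% | 490 |
| 0.5 | 0.75 | 13.4% | 595 |
| 0.7 | 0.51 | 28.6% | 875 |

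The last column treats records as independent.

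**4. What the conditional rule keeps.** If the threshold is p < 0.05, the share of the variance reduction retained is the part of E[z²] that lies beyond ±1.96: 2 × (1.96 × 0.0584 + 0.025) = 0.279. A simulation of 200,000 randomizations gave the same 28% at rho 0.3, 0.5 and 0.7.

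**5. Bias.** In that simulation the mean error of the unadjusted difference was about 0, as randomization implies. Given a moderate imbalance that the rule leaves alone (|z| between 1 and 1.96), the type I error of the unadjusted test was 5.7%, 7.4% and 8.9% at rho 0.3, 0.5 and 0.7. The expected shift in the six-week difference is rho × imbalance.

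**6. QALY scale, all inputs assumed.** With a utility SD of 0.10 to 0.25, the 95% limit of chance imbalance is 0.131 × SD = 0.013 to 0.033. Times rho of 0.3 to 0.7, this shifts the six-week utility by 0.004 to 0.023. Times 6/52 = 0.115 year, it is 0.0005 to 0.0027 QALY if only the six-week score is used. For comparison, a utility difference of 0.03 held for six weeks is 0.03 × 0.115 = 0.0035 QALY.

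**The case against.** **The article may be silent rather than wrong.** The rule speaks of important baseline characteristics, the list does not name EQ-5D, and the article condenses a fuller plan that is not shown. If EQ-5D falls outside the rule, how its baseline score is used could be settled there. The levels of the multilevel model are not named either, so a repeated-measures model that uses the baseline score is not excluded. This stands in part: nobody can say from the article that raw six-week scores will be compared. But the article does state a general rule for when covariates enter, the list is worded as open, and nothing exempts the baseline value of an outcome. The rule as published is a poor one for this variable.

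**The gain may be small.** Consent is obtained around 34 weeks of gestation (Recruitment), and the two scores are separated by birth, so rho may be low. This stands. At rho 0.1 there is almost nothing to gain, though at this sample size the adjustment also costs essentially nothing.

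**The QALY link is indirect.** The rule follows the regression models for the Table 2 outcomes, and the cost-effectiveness calculation is described separately. Applying the rule to QALYs is an inference.

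**A stronger reading that does not hold.** A reader might infer that small imbalances bias the QALY difference or pass into it in full. The documents do not support this. The randomized contrast is unbiased on average. The baseline score is taken before the six-week window opens and need not enter the QALY calculation, in which case an imbalance reaches the result only after multiplication by rho.

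**Conclusion.** The point holds as a matter of efficiency and pre-specification for one secondary outcome. As published, the covariate rule would seldom admit baseline EQ-5D and would make its entry depend on an undefined observed difference. The loss is precision, plus protection against error conditional on the imbalance that actually occurs; it is not bias on average.

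The size cannot be fixed from the documents. Over rho of 0.1 to 0.7 the available fall in standard error runs from negligible to more than a quarter. The conclusion that the rule forgoes most of that gain rests on reading the threshold as p < 0.05 or stricter. The relevance to QALYs rests on the further assumption that the same rule is applied there. The analysis of epidural use and the sample size of 992 are untouched.

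**What to change.** In Statistical analysis, add that the model for six-week EQ-5D always includes the baseline EQ-5D utility as a covariate, whatever imbalance is observed, and that this value is exempt from the imbalance rule. Add that where a QALY difference is estimated from the EQ-5D utility, it is adjusted for baseline utility in the same way. If the full analysis plan already says this, the article's rule only needs to be read alongside it.

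The cost is a sentence or two of text and one regression coefficient. The score is already collected, so no new data, visits or participants are needed. It should be fixed before outcome data are compared by arm.

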### Randomization

Once informed consent has been given, the participant will be asked to fill out some baseline questionnaires. Subsequently, participants will be randomly assigned (using sealed, blank envelopes) to either the intervention or the care-as-usual group. A list based on block randomization with a random block size, using https://www.randomizer.org, will be used for the order in which to fill the envelopes. Randomization will be stratified for different maternity care agencies to prevent the occurrence of any potentially confounding variables based on the location of the two agencies. Stratification will also be done for parity; this is an important determinant of use of EA with a two to three-fold higher uptake in primiparous women compared to multiparous women [12, 14].

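### The only stated covariate rule, triggered by imbalance between arms, would in practice keep parity, a stratification factor, out of the primary epidural model, at a modest and conservative cost

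*Protocol article*

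**What the plan says.** The Randomization section of the protocol article stratifies by maternity care agency, of which there are two, and by parity. On parity it states: "Stratification will also be done for parity; this is an important determinant of use of EA with a two to three-fold higher uptake" in first-time mothers.

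The Statistical analysis section lists parity among the baseline characteristics and says that the primary outcome, use of epidural analgesia (EA), "will be analyzed using multilevel logistic regression analysis". It names no covariates and does not say what the levels are. The one rule it gives for bringing in covariates is: "If important baseline characteristics will differ greatly between the study arms, we will include them in the analysis".

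The Sample size calculation section plans for a fall in EA use from 25% to 17%, "with an alpha 0.05 and beta 0.20", with 10% added for multilevel analysis and 10% for attrition, and concludes that "a sample size of 2 × 496 participants will be necessary".

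**The concern.** The design and the analysis rule pull against each other. Stratification exists to stop parity from differing between arms, while the rule lets a baseline characteristic in when it does differ. The one predictor that the protocol singles out as strongly related to the primary outcome is therefore the one least likely to qualify.

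When allocation is balanced on a strong predictor and the model ignores it, the model's standard error still contains between-parity variation that the allocation has removed from the treatment comparison. The test then rejects too rarely under the null, and precision that the design has secured goes unused. A rule that depends on the observed data, with no threshold for how large a difference counts, also leaves the covariate choice open until the data have been seen.

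**Working it through.** **Inputs from the protocol article.** EA 25% (control) and 17% (intervention); alpha 0.05; power 0.80; 10% multilevel inflation; 10% attrition; ratio of EA use, primiparous to multiparous, 2 to 3.

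**Assumptions.** The share of primiparous women is not given, so 35%, 45% and 50% are used. The odds ratio is taken to be the same in both parity groups, and overall rates are held at 25% and 17%.

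**Step 1: the plan's own figure.** Two proportions, two-sided, pooled variance under the null, no continuity correction: n = [1.96·√(2·0.21·0.79) + 0.842·√(0.25·0.75 + 0.17·0.83)]² / 0.08² = 405.7, so 406 per arm. Then 406 × 1.10 / 0.90 = 496.2. The stated 496 is reproduced. A one-sided test gives 320 × 1.10 / 0.90 = 391, which does not match.

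**Step 2: one case in full (ratio 3, 45% primiparous, 406 per arm).**

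- Control rates: multiparous 0.25 / (0.45·3 + 0.55) = 13.2%, primiparous 39.5%.
- Share of control-arm variance explained by parity: 0.45·0.55·(0.395 − 0.132)² / (0.25·0.75) = 0.091.
- Marginal log odds ratio: logit(0.17) − logit(0.25) = −0.487. The common within-parity log odds ratio that gives 17% overall is −0.529, with treated rates of 27.8% and 8.2%.
- Model standard error without parity: √[1/(406·0.25·0.75) + 1/(406·0.17·0.83)] = √(0.01314 + 0.01746) = 0.175.
- True sampling standard error under stratified allocation: each term is multiplied by one minus the variance share in that arm (0.091 control, 0.067 intervention), giving √(0.01314·0.909 + 0.01746·0.933) = 0.168. The ratio is 1.041.
- Type I error without parity: 2Φ(−1.96 / √(1 − 0.091)) = 4.0%.
- Power without parity: Φ[(0.487 − 1.96·0.1749) / 0.168] = 80.5%.
- With parity, the standard error of the log odds ratio is 0.182. Power is Φ(0.529/0.1824 − 1.96) = 82.6%.
- Equivalent number of women: [(1.96 + 0.940) / (1.96 + 0.858)]² = 1.058, or about 6% more.

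**Step 3: the range, at 406 per arm.**

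| Ratio | Primiparous | Variance explained | Model SE / true SE | Type I error, no parity | Power, no parity | Power, with parity | Equivalent extra women |
|---|---|---|---|---|---|---|---|
| 2 | 35% | 4.2% | 1.019 | 4.53% | 79.95% | 80.95% | 2.6% |
| 2 | 45% | 3.9% | 1.017 | 4.55% | 79.92% | 80.85% | 2.4% |
| 2 | 50% | 3.7% | 1.016 | 4.58% | 79.89% | 80.77% | 2.3% |
| 3 | 35% | 10.5% | 1.049 | 3.83% | 80.65% | 83.16% | 6.9% |
| 3 | 45% | 9.1% | 1.041 | 3.98% | 80.47% | 82.63% | 5.8% |
| 3 | 50% | 8.3% | 1.037 | 4.06% | 80.37% | 82.33% | 5.3% |

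At 446 per arm (496 less 10%, with no loss to clustering) power is 83.5 to 84.3% without parity and 84.3 to 86.5% with it.

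**Step 4: simulation.** With 8,000 trials per scenario and 45% primiparous, the model with parity had a type I error of 4.6 to 5.2%. At 446 per arm and ratio 3, the type I error was 4.2% without parity and 5.1% with it, and power was 85.4% and 87.2%.

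**Step 5: what adjustment does to the printed output.** The printed standard error of the log odds ratio rises slightly, from 0.175 to between 0.178 and 0.184. The log odds ratio moves from −0.487 to between −0.503 and −0.537. The test statistic grows because the estimate moves further than the standard error does.

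**The case against.** The strongest objection is that the article is a condensed text and no statistical analysis plan is shown. Silence about the list of fixed effects is no fault, and the rule says when a variable will be added, not that nothing else may be. That stands as far as it goes: the article does not state that parity is excluded. But it is not simply silent. It fixes one rule, parity is among the characteristics that the rule covers, and anyone applying that rule alone would leave parity out. The criticism is of the rule as written.

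It is also fair to say that validity is not at risk. Type I error is not inflated, the sample size reproduces from an unadjusted formula, and the unadjusted test delivers about the planned power.

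Several stronger readings are tempting but are not supported:

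- That parity can never enter. Incomplete blocks, or removals after the eligibility check noted under Table 1, could leave some imbalance. A great difference is very unlikely, not impossible.
- That the multilevel model uses the two agencies as its level and so cannot estimate their variance. No level is named, and in a multi-centre trial practices or hospitals are equally plausible.
- That the power loss is 3 points or more. Epidural rates of 50% and 20% by parity with 45% primiparous give 0.45·50 + 0.55·20 = 33.5% overall, which is not the planned 25%.
- That adjustment narrows the printed standard error. It does not, as Step 5 shows.

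**Conclusion.** The point holds as a matter of efficiency and pre-specification, not of validity. Following the stated rule would in practice omit parity from the primary model. The unadjusted standard error is too large only against its own true sampling error under stratified allocation, and the test is correspondingly conservative. Set against a model with parity, the loss in power is small, and the planned 80% is still roughly met.

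These sizes rest on the assumed 35 to 50% primiparous, the protocol's own two- to three-fold ratio, the planned 25% and 17%, and a common odds ratio across parity groups. A ratio near 2 puts the trial at the low end of the ranges, and a ratio near 3 at the high end. The conclusion is firm for parity. For agency it is weaker: the rule applies in the same way, but agency might already be represented in the multilevel structure, and the protocol gives no figure for how strongly it predicts EA use.

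**What to change.** For the primary EA model, replace the imbalance-triggered rule with a sentence stating that parity (primiparous or multiparous) and maternity care agency are included as fixed effects whatever balance is observed. With only two agencies, a fixed effect is the natural form.

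Do the same for secondary outcomes that have enough events to support the extra terms. It should not be imposed on very rare outcomes such as maternal death or uterine rupture, where added covariates can make the model fail to converge or give unstable estimates.

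The team should expect a slightly larger printed standard error and an odds ratio further from 1, and should not read that as a loss of precision. The cost is one sentence. Both variables are known at randomisation, and the sample size need not change.
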